### Data Collection

#### Patients

We will perform document analysis 3 (T3), 6 (T6), 9 (T9), and 12 (T12) months after a patient is included in the study. As part of these document analyses, we will conduct an intervention check to ascertain whether the CC-TRS is being carried out in adherence to the intervention protocol. Therefore, it will be possible to quantify the care received by patients. As part of the intervention, both patients and informal caregivers will discuss their experiences with the CC-TRS as part of their treatment plan evaluations with the CC team. This will be reported in patient files, thus offering the opportunity to gain insight into their experiences with the CC-TRS by conducting document analysis. We expect the CC-TRS to produce positive effects on somatic outcomes such as metabolic syndrome, cardiovascular risks, and (risk of) diabetes mellitus. Therefore, the following somatic outcomes of patients will be extracted from their medical files at baseline (T0) and after 12 months (T12): height, weight, BMI, waist circumference, systolic and diastolic blood pressure, lipid profile, and fasting blood glucose levels. Moreover, the presence of cardiovascular disease, diabetes mellitus, or hypertension will be registered, including the use of medications for these disorders.

There will be 3 face-to-face measurements: when patients are included in the study (T0), after 6 months (T6), and after 12 months (T12). The questionnaires used for quantitative data collection at T0, T6, and T12 are summarized in Table 1. The questionnaires *Consumer Quality Index* and *Experiences with CC-TRS* will only be administered at T12. At T12, after completion of all quantitative measurements, a 60-minute interview will be conducted with the patients. In this interview, a topic list will be used to discuss the results of the quantitative data, the course of the treatment, the implementation of the various treatment components, and the experiences of patients with the CC-TRS. Furthermore, patients will be asked which factors and specific aspects of the CC-TRS influenced the outcomes and whether the desired effects were achieved. All the interviews will be audiotaped and transcribed verbatim.

Patients will receive €7.50 (US $8.02) for each of the first 3 face-to-face measurements and €15 (US $16.04) for the fourth face-to-face measurement in the form of gift vouchers. In addition, their travel expenses will be reimbursed.

**Table 1 table1:** Quantitative measurements of patients at T0, T6, and T12.

Instrument	Description	Validity and reliability
CGI^a^	This is a 3-item scale and the most widely used brief assessment tool in psychiatry for measuring illness severity, global improvement or change, and therapeutic response [52,53].	The psychometric properties of CGI have not yet been established, but clinicians' ratings of psychiatric symptoms correlate significantly with self-rated and other valid scales of symptom severity [54]. Rating scales are an appropriate clinical technique for the measurement of change in antidepressant trials. Global improvement scales would be sufficiently sensitive toto distinguish between responders and nonresponders in clinical [55].
CQi^b^	This is a 15-item questionnaire that allows for the evaluation of outpatient treatment from patients’ perspectives [56].	Research has shown sufficient reliability (Cronbach α between .69 and .95) [57]. The CQi provides valid and reliable results in short-term care for patients in mental health care [58].
DES^c^	This is the Dutch version of the MHRM^d^, a 26-item questionnaire that measures recovery [59].	The Dutch version of the MHRM is a reliable measure (in terms of internal consistency) with a generally acceptable convergent and divergent validity. Cronbach α ranged from .86 to .94 [59].
Dutch PIH^e^	This is a Dutch translation 12-item questionnaire developed in Australia to measure self-management behavior and knowledge among patients with chronic diseases [60].	The PIH exhibits construct validity and internal consistency. Cronbach α is .82 [61]. The PIH has been translated and validated for use among Dutch patients with chronic obstructive pulmonary disease [60].
HoNOS^f^	The HoNOS is a structured interview measuring behavior, impairments, symptoms, and social functioning via the use of 12 items. The instrument has 3 addendums that measure manic symptoms, treatment motivation, and compliance with medication [62].	The Dutch version of the HoNOS has reasonably good psychometric qualities (intraclass correlation coefficient=0.92), can be administrated in a short period, is neither dependent on psychiatric diagnosis nor language, and is regarded as useful by both clinicians and patients [62].
MANSA^g^	This is a 16-item questionnaire that measures the quality of life, with a particular focus on satisfaction with life as a whole and with different life domains [63]. In addition to the MANSA, we will also ask patients to give a score between 0 and 10 to describe their quality of life in general.	The MANSA is a brief instrument for assessing quality of life focusing on satisfaction with life as a whole and with life domains. Its psychometric properties appear satisfactory (Cronbach α=.74 for the satisfaction rating) [63].
PANSS^h^	This is one of the most widely used instruments for measuring the presence and severity of positive, negative, and general psychopathological symptoms of schizophrenia. The PANSS is a 30-item structured interview [48].	The PANSS has good interrater reliability, adequate construct validity, high internal reliability, appropriate test-retest reliability, and external validity [48,64-66].
SDM-Q-9^i^	This is a self-report instrument comprising 9 items that was developed to measure patients’ perceptions of the shared decision-making process (SDM-Q-9) [67].	The SDM-Q-9 has a good acceptance, internal consistency, and acceptable to good convergent validity (Cronbach α=.88) [67].
SOFAS^j^	This is a 1-item rating (0-100) that assesses social and occupational functioning (independently of the severity of psychological symptoms) [50].	To our knowledge, the SOFAS has not yet been tested for psychometric quality. We will use this questionnaire to assess the criteria for treatment-resistant schizophrenia as established by the Working Group of the Treatment Response and Resistance in Psychosis. They use SOFAS to operationalize functional limitations [68].
Questionnaire experiences with treatment	This is a self-developed questionnaire containing 11 items about satisfaction with treatment in general and 4 items about satisfaction with treatment via the Collaborative Care program for patients with treatment-resistant schizophrenia.	The questionnaire has not been examined for psychometric quality.

^a^CGI: Clinical Global Impression.

^b^CQi: Consumer Quality Index (Geestelijke Gezondheidszorg en Verslavingszorg Ambulant).

^c^DES: Dutch Empowerment Scale.

^d^MHRM: Mental Health Recovery Measure.

^e^PIH: Partners in Health scale.

^f^HoNOS: Health of the Nation Outcome Scale.

^g^MANSA: Manchester Short Assessment of Quality of Life.

^h^PANSS: Positive and Negative Syndrome Scale.

^i^SDM-Q-9: Shared Decision-Making Questionnaire 9-item.

^j^SOFAS: Social and Occupational Functioning Assessment Scale.

#### Informal Caregivers

After 12 months (T12), informal caregivers’ experiences regarding both their role in the treatment and the degree of cooperation with the CC team will be measured via a Dutch translation of the *Family Perceptions of Caregiving Role* (FPCR) [69]. The FPCR is a 15-item questionnaire that measures collaboration between informal caregivers and care professionals. To the best of our knowledge, FPCR has not yet been examined for its psychometric quality. However, we consider this questionnaire to be suitable for measuring both the perceived collaboration between informal caregivers and the CC team and the former’s involvement in care. To measure the experiences of informal caregivers with respect to specific elements of CC-TRS, we will use a self-developed 15-item questionnaire called *Evaluation informal caregivers CC-TRS*.

Two 90-minute-long focus group interviews with informal caregivers will be conducted at T12. Given that patients could be enrolled at different points of the study, we plan to conduct focus group interviews as soon as possible after a sufficient number of patients have completed a full year of treatment with the CC-TRS. The focus group interviews will preferably take place with 6 to 12 informal caregivers, with a minimum of 4 people. In these focus group interviews, a topic list will be used, with topics referring to the overall experiences of the informal caregivers with the CC-TRS, its various components, and aspects of collaboration with the CC team. In the interviews, informal caregivers will also be asked to reflect on the perceived effects of the CC-TRS on the patients. The underlying principles of the CC-TRS will be discussed in conjunction with the specific features of CC-TRS that contribute to positive treatment outcomes. All interviews will be audiotaped and transcribed verbatim.

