#### Care Professionals

To compare team characteristics, we will describe the standard of care provided by the participating teams as well as the composition of staff before the start of the intervention period. To measure experiences with the training program, care professionals will complete an evaluation form after completing the training.

During the implementation of the CC-TRS, 90-minute feedback meetings will be held every 3 months with all care professionals in the team as well as the team manager. During these meetings, concrete information about the implementation achievements of the team will be discussed to promote the implementation and execution of the CC-TRS. In addition, factors that either promoted or hindered the implementation of the CC-TRS at the patient level will be discussed in an endeavor to both identify practical solutions to the barriers experienced and learn from each other by sharing successful applications of the CC-TRS. All these feedback meetings will be audiotaped and summarized, with notable quotes being transcribed verbatim.

For each patient, there will be a group interview with involved care professionals at T12. Within this 1-hour group interview, the individual case will be discussed in detail with care professionals. A quantitative measure will form the input for this interview. In addition, a topic list will be drawn to discuss the process of implementation of the CC-TRS within that specific case and to explore associations between the implementation process and patient outcomes. All interviews will be audiotaped and transcribed verbatim.

The quantitative data will be entered into SPSS Statistics (version 26; IBM Corp). The transcribed texts from the qualitative interviews and feedback meetings will be entered into MAXQDA (version 2020).

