### Analyses

We will perform a combination of qualitative and quantitative analyses in accordance with the method described by Stake [45]. In this multiple case study, the analysis of data will occur at 2 different levels: the individual case level (single-case analysis) and group level (cross-case analysis).

In the single-case analysis, data from different sources and perspectives will be analyzed for each individual case. On the basis of the document analysis; quantitative measurements; and interviews with patients, informal caregivers, and care professionals, we will draw up a comprehensive description of each case in order to gain insight into how the CC-TRS was offered to each individual patient, how this was experienced by different people (patients, informal caregivers, and professionals), the course of the treatment over time, and individual patient’ outcomes over time. For each case, we will examine which factors (CC-TRS-related and other) contribute to both positive and negative treatment outcomes. By integrating data at the case level, we can examine the factors that influence the effective application of the CC-TRS at the following levels: (1) treatment-related variables, (2) patient variables, (3) caregiver variables, (4) informal caregiver variables, (5) interactional variables, (6) organizational variables, and (7) other contextual variables. The single-case analysis will result in a detailed description of the relevant case, including tables with a summary of the findings in relation to our aforementioned research questions.

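### The one caregiver focus-group topic that ties programme features to outcomes covers positive outcomes only, although the case analysis it feeds must explain positive and negative outcomes

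*Protocol article*

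**What the plan says.** Under Data Collection, Informal Caregivers, two 90-minute focus groups are planned, guided by a topic list that the article summarises but does not reproduce. The summary has three parts:

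- general topics, "with topics referring to the overall experiences of the informal caregivers with the CC-TRS, its various components, and aspects of collaboration with the CC team";
- a question on effects, in which "informal caregivers will also be asked to reflect on the perceived effects of the CC-TRS on the patients";
- a topic linking features to outcomes: "The underlying principles of the CC-TRS will be discussed in conjunction with the specific features of CC-TRS that contribute to positive treatment outcomes".

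Under Analyses, the caregiver interviews are one of several sources for each case: from records, measurements and "interviews with patients, informal caregivers, and care professionals, we will draw up a comprehensive description of each case". The aim is then stated in two directions: "For each case, we will examine which factors (CC-TRS-related and other) contribute to both positive and negative treatment outcomes".

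**The concern.** The third focus-group topic takes benefit as given. Caregivers are invited to say which features produced good results. No matching topic is described for features that had no effect or an unfavourable one. An analysis meant to explain both kinds of outcome would then receive caregiver input on the explanatory question in one direction only.

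This matters because the caregiver accounts are explanatory evidence. The last research question asks how the effects can be explained by the implementation process and by the experiences of patients, caregivers and professionals. The study has 20 patients and describes no comparison group, so linking an outcome to a programme feature depends heavily on the qualitative material. The Objectives section says the results will be used to improve the programme further, which requires knowing which features failed as well as which worked. The authors also say that they expect benefit, and that is a further reason for balanced questions.

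**Working it through.** No arithmetic applies: the point concerns the wording of a qualitative topic and depends on no sample size, effect size or test. The check sets each source beside what the single-case analysis needs, namely a link from a feature or factor to an outcome, in either direction.

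| Source | What it asks | Links features or factors to outcomes? | Direction |
|---|---|---|---|
| Caregiver focus groups, general topics | Experiences, components, collaboration | Not as described | Open |
| Caregiver focus groups, effects | Perceived effects on the patient | Effects only, not which feature caused them | Open |
| Caregiver focus groups, features | Features behind outcomes | Yes | Positive only |
| Caregiver questionnaires | Collaboration and involvement (FPCR); experience with specific elements (self-developed) | Not as described | Not stated |
| Treatment-plan evaluations in patient files | Patient and caregiver experiences, read by document analysis at 3, 6, 9 and 12 months | Not as described | Open |
| Patient interview at 12 months | "patients will be asked which factors and specific aspects of the CC-TRS influenced the outcomes and whether the desired effects were achieved" | Yes | Open |
| Professionals' feedback meetings | "factors that either promoted or hindered the implementation of the CC-TRS at the patient level will be discussed" | Factors to implementation | Both |
| Professionals' group interview at 12 months | Associations between implementation and patient outcomes | Yes | Open |

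Three things follow.

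1. Among the caregiver sources, only one topic is described as asking for the link that the analysis needs, and it is limited to positive outcomes.
2. The corresponding topics for patients and professionals carry no such limit. The asymmetry is confined to the caregivers.
3. The open caregiver topics compensate only in part. Saying that a patient got worse, or that a component was a burden, is not the same as being asked which feature led to an unfavourable result. A caregiver may volunteer that link, but no described topic asks for it.

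**The case against.** The strongest reply is that one summary sentence is being asked to carry too much. The topic list is not shown, and the sentence describes what will be discussed rather than how a question will be put. The full list may be balanced. The same groups cover overall experience and perceived effects without direction, so a caregiver who saw harm has room to say so. Negative factors can also reach the case analysis through patients, professionals and records.

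Most of this stands, and it rules out three stronger readings that a reader might infer.

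- *That the caregiver evidence as a whole is steered towards benefit.* One topic among several has this wording. The open topics, the questionnaires and the patient files all leave room for unfavourable reports.
- *That the focus groups are the only qualitative source on caregivers.* The Patients subsection of Data Collection says that caregivers' experiences are also discussed in treatment-plan evaluations and recorded in patient files for document analysis. Those discussions take place with the treating team, so they are not an equivalent setting for criticism, but they do exist. The focus groups are the only dedicated caregiver interviews.
- *That silence about harm will be read as absence of harm.* Nothing in the Analyses section says so. It describes integration across several sources.

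The point about the unseen list does not remove the finding. The article affirmatively describes this topic in one direction. If the list is two-sided, the sentence misdescribes it. If the list follows the sentence, it is narrower than the analysis requires.

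**Conclusion.** The mismatch is real and minor. The one described caregiver topic that links programme features to outcomes is confined to positive outcomes, while the analysis it feeds must explain both directions. Unfavourable links may therefore be under-elicited in these interviews. That they will be is not shown.

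The size cannot be estimated from the article. The wording applies to both planned focus groups but to one topic within them. It affects no calculation, including the Friedman tests on patient outcomes. The conclusion assumes that the article's summary reflects the topic list reasonably well.

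**What to change.** Reword the caregiver topic so that it asks which features of the programme helped, which made no difference, and which made things worse, for the patient or for the caregiver. Put the unfavourable part explicitly in both groups. This brings the topic into line with the two-directional aim in the Analyses section. If the existing list is already two-sided, correct the sentence in the article instead. The patient and professional topics can stay as they are.

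The cost is one line in the topic list and a little of the 90 minutes. The section on COVID-19 modifications places the caregiver group interviews in October 2022, after publication in June 2022, so on that date the change could precede data collection. If a group has already been held with the positive-only topic, say so when reporting the caregiver findings.

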#### Care Professionals

To compare team characteristics, we will describe the standard of care provided by the participating teams as well as the composition of staff before the start of the intervention period. To measure experiences with the training program, care professionals will complete an evaluation form after completing the training.

During the implementation of the CC-TRS, 90-minute feedback meetings will be held every 3 months with all care professionals in the team as well as the team manager. During these meetings, concrete information about the implementation achievements of the team will be discussed to promote the implementation and execution of the CC-TRS. In addition, factors that either promoted or hindered the implementation of the CC-TRS at the patient level will be discussed in an endeavor to both identify practical solutions to the barriers experienced and learn from each other by sharing successful applications of the CC-TRS. All these feedback meetings will be audiotaped and summarized, with notable quotes being transcribed verbatim.

For each patient, there will be a group interview with involved care professionals at T12. Within this 1-hour group interview, the individual case will be discussed in detail with care professionals. A quantitative measure will form the input for this interview. In addition, a topic list will be drawn to discuss the process of implementation of the CC-TRS within that specific case and to explore associations between the implementation process and patient outcomes. All interviews will be audiotaped and transcribed verbatim.

The quantitative data will be entered into SPSS Statistics (version 26; IBM Corp). The transcribed texts from the qualitative interviews and feedback meetings will be entered into MAXQDA (version 2020).

### Analyses

We will perform a combination of qualitative and quantitative analyses in accordance with the method described by Stake [45]. In this multiple case study, the analysis of data will occur at 2 different levels: the individual case level (single-case analysis) and group level (cross-case analysis).

In the single-case analysis, data from different sources and perspectives will be analyzed for each individual case. On the basis of the document analysis; quantitative measurements; and interviews with patients, informal caregivers, and care professionals, we will draw up a comprehensive description of each case in order to gain insight into how the CC-TRS was offered to each individual patient, how this was experienced by different people (patients, informal caregivers, and professionals), the course of the treatment over time, and individual patient’ outcomes over time. For each case, we will examine which factors (CC-TRS-related and other) contribute to both positive and negative treatment outcomes. By integrating data at the case level, we can examine the factors that influence the effective application of the CC-TRS at the following levels: (1) treatment-related variables, (2) patient variables, (3) caregiver variables, (4) informal caregiver variables, (5) interactional variables, (6) organizational variables, and (7) other contextual variables. The single-case analysis will result in a detailed description of the relevant case, including tables with a summary of the findings in relation to our aforementioned research questions.

In the cross-case analyses, the findings from the 20 single-case analyses will be analyzed at the group level. In 3 ways, we will investigate the extent to which the implementation plans were successfully carried out. First, we will conduct an intervention check through document analysis. In this way, we systematically identify if and to what extent the interventions have been implemented. Second, we will discuss, through feedback meetings with team members, which components of the CC-TRS are implemented as planned and which components are not, whether all preconditions are met sufficiently, and discuss the teams’ needs to overcome experienced barriers regarding implementation. Feedback meetings will be audiotaped and summarized, with notable quotes being transcribed verbatim. Third, in supervision meetings, CNS and CC nurses will discuss their own considerations and explanations for the extent and manner in which interventions are implemented at the patient level. Noteworthy findings and considerations will be noted. We will quantitatively analyze the overall effects of CC-TRS on different outcome measures. To this end, exploratory analyses will be performed on patients (n=20) using the Friedman Test (nonparametric variant of the repeated measures analysis of variance). Next, we will descriptively analyze the quantitative data related to patients’ satisfaction with the CC-TRS program, by using the *Consumer Quality Index* and the questionnaire *Experiences with CC-TRS*. Following this, an overall analysis of individual interviews with patients will be conducted. Descriptive qualitative analyses will then be performed to explore the experiences of patients in the CC-TRS intervention program. Subsequently, the data from informal caregivers will be analyzed, first quantitatively (FPCR and the questionnaire *Evaluation informal caregivers CC-TRS*), followed by a qualitative descriptive analysis of the data generated in the focus group interviews. The next step will be to analyze the data pertaining to care professionals. The first quantitative analysis will be conducted on caregivers’ satisfaction with the training program. This will be followed by a qualitative analysis of the data generated through feedback meetings. Finally, data from the caregivers’ interviews will be descriptively analyzed. Through recourse to the method of content analysis [70], patient records will be analyzed to investigate the implementation of the CC-TRS.

The final step in the cross-case analysis will involve the integration of both qualitative and quantitative findings through the use of summary descriptions and tables drawn up in previous stages of the data analysis. In addition, the experiences of the patients, informal caregivers, and professionals will be presented at the group level. On the basis of our analyses, we will be able to describe the extent to which the CC-TRS was implemented and the factors determining its successful implementation. At both the individual and group levels, we will provide insight into the preliminary effects of the intervention, including the factors that contributed to these effects.

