#### Sample Size

To gain insight into the implementation process of the CC-TRS, the factors influencing this implementation and preliminary effects at the patient level, sufficient variation in patient characteristics, caregiver characteristics, and the context of implementation are needed. Within the context of the 2 FACT teams and an EIT, we believe that it will be sufficient to include 20 patients in our study to achieve the desired variation. If patients decide to stop the CC-TRS interventions, they will be asked to remain in the study purely for the purpose of carrying out a follow-up analysis.

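### The Friedman test, the only inferential test named for effects, does not fit the two-visit somatic outcomes or the CGI change items, and for the three-visit scales it needs complete data and gives no size of change

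*Protocol article*

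**What the plan says.** Under Analyses, the cross-case part states: "We will quantitatively analyze the overall effects of CC-TRS on different outcome measures". The method follows at once: "exploratory analyses will be performed on patients (n=20) using the Friedman Test (nonparametric variant of the repeated measures analysis of variance"). No other inferential test for effects is named. Satisfaction measures are handled descriptively.

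Under Data Collection, Patients, the face-to-face measurements take place "when patients are included in the study (T0), after 6 months (T6), and after 12 months (T12"). The somatic measures follow a different schedule: "the following somatic outcomes of patients will be extracted from their medical files at baseline (T0) and after 12 months (T12"). Research question 5 counts somatic comorbidities among the outcomes on which preliminary effects are sought.

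Table 1, headed as covering T0, T6 and T12, describes the CGI as a "3-item scale and the most widely used brief assessment tool in psychiatry for measuring illness severity, global improvement or change, and therapeutic response".

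Under Sample Size, the number is a judgement about variety between cases: "we believe that it will be sufficient to include 20 patients in our study to achieve the desired variation". Of patients who stop the interventions it says that "they will be asked to remain in the study purely for the purpose of carrying out a follow-up analysis". No dropout rate is given.

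**The concern.** The test and the schedule are both stated, so whether they match can be judged from the article itself. Four features do not match well.

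- **Two time points.** The Friedman test ranks values within each patient. With only T0 and T12 the rank records whether the value went up or down and nothing else. A weight loss of 1 kg and one of 15 kg count the same.
- **Complete blocks.** With three visits, a patient lacking any one of them leaves the test for that outcome. The n=20 attached to the test then holds only if nobody misses a visit.
- **Output.** The test yields an omnibus p-value. Research question 5 asks what the preliminary effects are, which needs a size of change and its uncertainty.
- **CGI items.** An item rating improvement or response needs an earlier state to compare with. At T0 the programme has not begun, so there is no value to rank.

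At stake is how much 20 intensively studied patients can show about preliminary effects, and whether the reported n describes the data actually analysed.

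**Working it through.** **Inputs from the article.** n = 20 (Sample Size; Analyses); k = 3 visits for the scales and k = 2 for somatic outcomes (Data Collection, Patients). Effect size, correlation and missingness are not given, so the values below are assumptions. The 20 itself cannot be re-derived, because it rests on variation between cases and not on a power calculation.

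**1. Somatic outcomes, k = 2.** Without ties, the Friedman statistic is (n₊ − n₋)²/n, where n₊ and n₋ count patients who rise and fall. This is the sign-test chi-square.

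- 15 of 20 in one direction: (15 − 5)²/20 = 5.0, above 3.84; exact two-sided p = 0.041.
- 14 of 20: (14 − 6)²/20 = 3.2, below 3.84; exact p = 0.115.

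So at least 15 of 20 must move the same way. Power, for normally distributed changes with standardised change d (mean change divided by the SD of the changes), two-sided 0.05: the chance that one patient moves in the true direction is Φ(d). For d = 0.5, Φ(0.5) = 0.691, and the chance of 15 or more of 20 (or 5 or fewer) is 0.384. Wilcoxon values are simulated.

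| Assumed d | Friedman, k = 2 | Wilcoxon signed-rank |
|---|---|---|
| 0.5 | 0.38 | 0.55 |
| 0.65 | 0.59 | 0.77 |
| 0.8 | 0.77 | 0.92 |

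**2. Three-visit scales, complete blocks.** If T6 and T12 are each missing independently with probability m, the expected number of complete patients is 20(1 − m)²; the number with a given pair, such as T0 and T12, is 20(1 − m).

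| Assumed m | Complete for Friedman | Available T12-T0 pairs |
|---|---|---|
| 5% | 18.1 | 19 |
| 10% | 16.2 | 18 |
| 15% | 14.4 | 17 |
| 20% | 12.8 | 16 |

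If the only loss is dropout before T12, 5% and 10% leave an expected 19 and 18. All 20 are then retained with probability 0.95²⁰ = 0.36 and 0.90²⁰ = 0.12. Simulated Friedman power (assumed means 0, 0.3 and 0.6 SD, correlation 0.6) falls from 0.60 at n = 20 to 0.42 at n = 14.

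**3. CGI.** Severity can be rated at all three visits. Improvement and response can be rated at T6 and T12 only, which leaves two usable values and no three-visit block.

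**4. Is Friedman a poor choice for the three-visit scales?** Complete data, n = 20, correlation 0.6, normal errors, simulated:

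| Assumed means at T0, T6, T12 (SD) | Friedman | Categorical-visit test (Hotelling) | Paired t, T12-T0 |
|---|---|---|---|
| 0, 0.25, 0.5 | 44% | 53% | 66% |
| 0, 0.5, 0.25 | 44% | 53% | 22% |

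The large gap to the paired contrast appears only when change is steady. Against another omnibus test the gap is about 9 points. With heavier-tailed errors (linear trend, separate simulation) the order reverses: Friedman 60% against 57% for Laplace errors, and 71% against 65% for t errors with 3 degrees of freedom.

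**The case against.** The best defence is that this is an exploratory case study. The 20 patients were chosen for variety, the Objectives disclaim quantitative generalisation, and the single-case analyses describe each patient's outcomes over time, so a patient with a missed visit still contributes there. For short ordinal scales in about 20 patients a rank test is reasonable, as step 4 shows. This stands: there is no case for requiring that Friedman be replaced on the three-visit scales.

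It is also fair that the article does not list the somatic outcomes under the Friedman test. That reading is an inference from its reference to different outcome measures and from research question 5. But no other test is offered for them. Likewise, the heading of Table 1 is not a strict schedule, since it also covers two questionnaires given only at T12. The text restricts those two explicitly, however, and does not do so for the CGI items.

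Descriptive summaries and intervals may sit in a fuller plan. That would answer the point on size of change, but it would not alter what the named test requires or what it becomes with two time points.

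Two stronger readings are tempting and are not supported. A reader might infer that the analysis cannot have 20 patients; that follows only if visits are missed, and no rate is given. The somatic and CGI points cost power or interpretability, not patients. A reader might also infer that patients who stop the programme are excluded. They are asked to stay for follow-up, and one measured at T0, T6 and T12 is a complete block and is analysed.

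**Conclusion.** The concern holds in a limited form. The firmest part is the somatic outcomes: if the named test is applied to them, it is a sign test, needs 15 of 20 in one direction, and has power of about 0.38 against 0.55 for Wilcoxon at an assumed standardised change of 0.5 with normal changes. The CGI point is certain for the T0 rating and affects only the improvement and response items. The loss of patients on the three-visit scales is conditional: none if no visit is missed, and about 14 of 20 left if 15% are missing independently at each of T6 and T12. The omnibus test by itself does not supply the size of change that research question 5 needs. Because the analyses are exploratory, this weakens what can be learned without invalidating the study, and the remedy is cheap enough to be worth making.

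**What to change.** Amend the Analyses text as follows.

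- **Measured somatic values (T0, T12):** Wilcoxon signed-rank test with the Hodges-Lehmann estimate and 95% interval.
- **Scales at T0, T6, T12:** keep Friedman as the exploratory omnibus test. Add T6-T0 and T12-T0 paired changes with 95% intervals, using every patient who has the relevant pair. A mixed model with visit as a category is an optional sensitivity analysis.
- **CGI:** test only severity across three visits; summarise improvement and response at T6 and T12.
- **Numbers:** replace the blanket n=20 with the number analysed for each outcome and visit.

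The cost is a few lines of text, a little more analysis and more exploratory contrasts to report. No extra data collection is needed.
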